## **Economic analysis**

Changes to both health outcomes and to economic costs from a larger adoption of the supporting self-management project may be estimated with cost-effectiveness analysis. A health sector perspective will be adopted and values collected for variables that describe the participant's use of hospital health services during the timeframe of the study. This will include data from emergency presentation and inpatient admissions. These costs will be valued using market prices, or shadow prices will be imputed. The cost of delivering the H4U service will be assessed by measuring and valuing the resources used [53]. The intervention costs will be calculated, factoring in staff time involved in being trained, and in delivering the interventions. Also included will be any overhead costs and costs of sessions provided. For the group intervention the costs will be divided over the attendees.

Changes to health benefits will be assessed through the use of quality-adjusted life-years. The SF-12 Health Survey can be converted to short form 6-dimension (SF-6D) which allow for utility values to be calculated [49]. To calculate the quality-adjusted life years (QALY) gain over the entire follow-up period an 'area under the curve' methodology will be used [53]. As costs are likely to be higher for one group compared to the other, and QALY gains may differ, an incremental cost-effectiveness ratio can be constructed to show the cost per extra QALY gained [53]. There will be uncertainty around cost and QALY estimates and this will be explored using cost-effectiveness planes generated from 1,000 bootstrapped resamples of the data for each of the three comparisons. Finally, we will generate cost-effectiveness acceptability curves, using the net-benefit approach and bootstrapping, to indicate the probability that any of the three approaches is the most cost-effective for different values placed on a QALY gain.

Within a project of this size significant differences in quality of life between the groups may not be seen, however, collecting data will provide an estimation of the baseline quality of life in this patient population. Cost-effectiveness acceptability curves can be plotted and used to inform decisions around widespread adoption of this method.

Longer terms costs and quality-adjusted life-years will be modelled using a decision analytic Markov model. The advantage of using the Markov model is that we can extrapolate beyond the data collection period and describe longer term costs and benefits of the intervention. While this method enables longer term costs and outcomes of the intervention to be forecast, the decision uncertainty will increase. To appropriately quantify uncertainty, Monte Carlo re-samples will be drawn from probability distributions specified for all model parameters.

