- 188                   • All participants will be offered a survey to complete as part of process evaluation  
189                   (appendix 5). This survey will be distributed at the follow-up session and can also be  
190                   completed online via survey monkey, and/or mail out copies.
  
- 191                   • Participants who withdraw from the study who wish that their data is not included in the  
192                   analysis will be required to complete a withdrawal of consent form.

193

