### *Intervention*

The intervention group will receive the blend of MI and CBT. This model of patient-centred self-management support, delivered as an office-based program through telephone calls has demonstrated successful outcomes for similar populations [19,22,38-9]. A member of the project

team will facilitate the MI/CBT intervention via the telephone. The individual who will deliver the telephone support is a registered healthcare practitioner through the Australian Health Practitioner Regulating Authority (APHRA). He has attended a 2-day workshop on MI and has received additional coaching from [name] [name], who is a nationally endorsed Health Psychologist and Sport and Exercise Psychologist who has been registered and practicing as a Psychologist since 1998. The individual who will deliver the intervention also delivered 144 hours of MI-CBT during the H4U trial.

Each participant will receive 5 phone calls, each lasting up to 20 minutes. Telephone support following a CBT approach, bedded in MI philosophy has shown to be effective in behaviour modification [38-9]. Participants will receive 4 calls over a 6-week period, with a 'booster' call at 12 weeks. In terms of incorporating the MI/CBT blend, MI will be utilised for sessions 1 to 3, as MI is identified as an effective tool for behaviour change initiation [21]. From session 3 to session 5 a blend of MI/CBT will be used, as CBT is an action orientated treatment [21, 23-4].

As part of self-management support, participants, where the intervention is appropriate, will be made aware of programs aimed at lifestyle risk modification existing in the community. Following the MI/CBT theory, no mandatory referrals will be made to these programs, however the facilitator may highlight the existence of these programs should the situation warrant it. The facilitators will be aware of the programs that are available in the community and can make appropriate referral to the programs on behalf of the participants. This pathway may highlight to participants the range of programs that are available in the community. Utilizing existing programs in the community may be of benefit to the participants, while it also encourages service co-ordination and avoidance of service duplication.

*Control*

242 All control group participants will attend the briefing session so they will receive the same  
243 educational material around lifestyle risk factor modification as group 1 from that session.

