**Sample Size and Statistical Analysis**

To compare differences in our outcome measures a series of 3 x 2 mixed model ANOVAs will be undertaken. Utilizing data from the H4U study, to detect an effect size of 0.35 or greater, with the alpha set at .05, and the power set at .90, a sample size of 50 participants per arm will be required. Protecting against a drop-out rate of 20% over the 9 month period, 68 participants will be recruited and randomized into each arm. The study therefore aims to recruit approximately 136 participants.

A full intention-to-treat principle will be used. For participants with missing data at 3 month and 9 month the last-observation-carried forward approach will be adopted (Shao and Zhong, 2003). Repeat sensitivity analyses will be undertaken to provide indication that the imputed values have a significant effect on the outcome.

313

314 **Process measures**

315 The project team will log the number of referrals made by the surgeons in Specialist Clinic. The  
316 project team will record patient feedback regarding interest and opinions on the project, which is  
317 hoped may give insight into future program development strategies.

318 A log will be maintained of how many project participants contact the project team during the  
319 intervention phase, the reason for contact, the method of contact and the outcome. During any  
320 non-structured contact no intervention is to be delivered at that time.

321 To examine the acceptability of the H4U study, participants allocated to the intervention group  
322 will also be administered an additional questionnaire, after the 9 months follow up. This  
323 questionnaire will include items addressing satisfaction with the components of the project, their  
324 perceived utility of the intervention. The questionnaire will also address whether participants  
325 attended a community health program, and the frequency of visits. To obtain a more in-depth  
326 understanding of the potential barriers and facilitators at the service delivery and individual level  
327 to uptake of this programme, we will also conduct semi structured interviews with a subsample  
328 of participants in the intervention group. Recruitment for the interviews will be purposive to  
329 maximise variation such as urban/rural location, gender and age for patients. Sampling will  
330 continue until no new themes or categories emerge from the data (the so-called thematic  

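### The economic analysis is labelled health sector but costs only hospital use plus programme delivery; community-programme use is left out and is described for one arm only

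*Protocol*

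**What the plan says.** The Economic analysis section of the Protocol sets the scope of costs in one sentence: "A health sector perspective will be adopted and values collected for variables", and the variables it goes on to specify are those on each participant's use of hospital services. The next sentence gives the content: "This will include data from emergency presentation and inpatient admissions". Delivery of the programme is costed as well: "The intervention costs will be calculated, factoring in staff time involved in being trained, and in delivering the interventions", together with overheads and the cost of sessions. Benefits are QALYs from the SF-12 converted to SF-6D. The two are combined in an incremental cost-effectiveness ratio (ICER) and in acceptability curves meant to inform wider adoption.

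In the Intervention section, facilitators make intervention participants aware of community lifestyle programmes where appropriate, and "can make appropriate referral to the programs on behalf of the participants". Referral is not compulsory. The Control section gives the control arm the same briefing session and, after that, only a reminder about follow-up attendance.

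Under Process measures (within Sample Size and Statistical Analysis), an additional questionnaire is described: "To examine the acceptability of the H4U study, participants allocated to the intervention group" receive it after the 9-month follow-up. It asks whether they "attended a community health program, and the frequency of visits". The stated purpose is acceptability, and no link to costing is made. Separately, the Recruitment section says: "All participants will be offered a survey to complete as part of process evaluation". The content of that survey is in an appendix that is not shown.

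**The concern.** A health-sector perspective would ordinarily cover health services outside the hospital, at least those that the intervention may change. Here the label is wider than the service use collected. The gap includes a service on the intervention's own pathway: the facilitator can send participants to community programmes, and the Protocol expects that these may benefit them.

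Any such benefit that reaches the SF-12 enters the QALY side of the ratio, while the cost of the programmes does not enter the cost side. The one measurement that could repair this is described for the intervention arm only. This is a matter of what data are gathered and from whom, so a later analysis plan could not recover control-arm use that was never asked about.

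At stake are the incremental cost, the ICER and the acceptability curves. The longer-term Markov model would also be affected in so far as it draws on the trial's costs.

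**Working it through.** The Protocol gives no cost, visit count or ICER, so there is no figure to reproduce. The check sets the passages side by side and then examines the direction of error algebraically.

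**Step 1. What is costed and what is measured, by arm, as described**

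| Item | Costed? | Measured in intervention arm? | Measured in control arm? |
|---|---|---|---|
| Hospital use (emergency and inpatient named) | Yes | Yes | Yes |
| Programme delivery (training, staff time, overheads, sessions) | Yes | Yes | Briefing session only, where costed |
| Community-programme visits | Not named | Yes, additional questionnaire | Not described |
| Primary care | Not named | Not described | Not described |

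**Step 2. Direction of error**

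Let c be the cost of one community-programme visit, vI and vC the mean visits per participant in the intervention and control arms, and s any fall per intervention participant in the cost of other uncosted non-hospital care.

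- True contribution to incremental cost: c(vI − vC).
- Error if omitted in both arms (the plan as written): 0 − c(vI − vC) = −c(vI − vC).
- Error if counted in the intervention arm only: c·vI − c(vI − vC) = +c·vC.
- Error if all non-hospital care is omitted: −[c(vI − vC) − s].

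A negative error understates incremental cost and favours the intervention.

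**Step 3. Illustration**

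Visit counts are assumed. Results are in units of one visit cost per participant (c = 1).

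| vI | vC | True contribution | Error, omitted in both arms | Error, intervention arm only |
|---|---|---|---|---|
| 1 | 1 | 0 | 0 | +1 |
| 2 | 1 | +1 | −1 | +1 |
| 4 | 1 | +3 | −3 | +1 |
| 8 | 2 | +6 | −6 | +2 |
| 1 | 2 | −1 | +1 | +2 |

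With two extra visits in the intervention arm (vI − vC = 2) and all non-hospital care omitted:

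- s = 0: −(2 − 0) = −2
- s = 1: −(2 − 1) = −1
- s = 2: −(2 − 2) = 0
- s = 4: −(2 − 4) = +2

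The omission can thus understate incremental cost, leave it unchanged or overstate it. Understatement needs c(vI − vC) to exceed s. Asking one arm only does not itself produce that understatement; it prevents its correction, and it would produce the opposite error if those visits were costed without a control counterpart.

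**The case against.** The strongest case against has five parts.

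- **Bias is not shown.** A reader might infer that incremental cost is definitely biased in favour of the intervention because its calls generate programme use. The documents do not support that. Referral is optional, and the Briefing Session section has a community-programme speaker whom both arms hear, so the between-arm difference in use may be small. Step 3 shows that the error can be zero or change sign. This objection stands, and the point is worded conditionally.
- **The omission may look large beside the intervention.** Call time is at most 5 × 20 = 100 minutes per participant, so a reader might infer that the missing cost exceeds the counted one. That does not follow: training, overhead and session costs are also counted, and the Protocol supplies no prices or visit numbers.
- **The list may not be exhaustive.** The sentence naming emergency and inpatient data is inclusive, and hospital outpatient visits could fall within it. True, but the sentence before it confines service use to hospital services, so community programmes and primary care remain outside.
- **The control arm may be asked elsewhere.** The survey offered to all participants is not shown, so this cannot be ruled out. However, Process measures places the attendance items in the additional intervention-arm questionnaire.
- **The economic analysis is secondary and tentatively worded.** This limits the weight of the point. It remains a stated aim of the study, with results intended for adoption decisions.

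**Conclusion.** The point holds in conditional form. The stated perspective is wider than the costs collected, which are hospital use plus programme delivery. Community-programme use, which the facilitator may prompt in the intervention arm, is not costed, and as described it is recorded in that arm alone, so no between-arm cost difference can be formed.

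Incremental cost may be understated by c(vI − vC) − s per participant when that quantity is positive. A positive value is plausible because only the intervention arm has a facilitator referral route, but it is not established. The size cannot be given, since the document states none of c, vI, vC or s. The conclusion assumes that the survey offered to all participants does not already carry these items. It should be dealt with before the result is presented as a health-sector ICER; it does not touch the primary comparison of physical activity.

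**What to change.** Ask the programme-attendance and visit-frequency items, with primary care use, in the same form and at the same time in both randomised arms. The process survey already offered to everyone is a natural place. Name these items in the Economic analysis section as costed resources and give the source of their unit costs. The cost is slight response burden, recall error over a period of up to nine months, and some work to obtain unit prices. Survey items cannot reach the medical-record audit cohort, so this remedy serves the comparison of the two randomised arms only.

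If both arms cannot be asked, restate the perspective as hospital plus programme delivery cost wherever it appears, and make no health-sector claim from the ICER or the acceptability curves. This costs nothing beyond a narrower conclusion. In that case the intervention-arm attendance data should stay descriptive and not be added to the costs of one arm.

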## **METHODS AND ANALYSIS**

### **Design**

The H4U-2 project is a randomised controlled trial with assessment of outcomes at three points- baseline, post 12 weeks and 9 months designed and reported in line with the CONSORT recommendations for reporting (Figure 1). The study will be conducted at large regional tertiary public hospital that's serves a wide geographical region, with a socioeconomically diverse population. A total of 136 patients who present to BH Specialist Clinic as an elective admission will be recruited and included in the project (figure 1). The trial will be registered with the Australian and New Zealand Clinical Trials Registry prior to patient recruitment. The study will commence 01/12/18 and commence 01/12/22.

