### **Randomisation**

Participants who fulfil the inclusion criteria and consent to take part in the trial will randomised to either the intervention or the control group based on a random number sequence produced by a computer generated program (randomizer.org). Assignments will be prepared and sealed in sequentially numbered opaque envelopes. Assignment will be made by opening the next envelope in the sequence, after the recruiter determines eligibility for the study, participants

consent to take part, and baseline measurements are completed.

[figure not shown]

Figure 1: CONSORT Flow Chart

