### *Self-Efficacy*

Self-Efficacy to be physically active will be measured via a physical activity self-efficacy survey. This survey has been built upon previous research, with modifications to suit the target group that this study proposes [44]. The survey measures confidence related to completing physical activity while faced with recognised barriers to physical activity completion.

290 *Medical Outcomes Study Short Form 12 Health Survey (SF-12)*

291 To measure quality of life the Medical Outcomes Study Short Form 12 Health Survey (SF-12)  
292 will be used [49]. The SF-12 was derived from twelve questions of the SF-36, which make up  
293 the MCS (Mental Component Summary) and PCS (Physical Component Summary). The survey  
294 can be administered in two to three minutes, which saves both time and resources in large-  
295 scale population surveys. The SF-36 has been validated in an Australian population 3. The two  
296 scores range between 0 and 100, with increasing values equating to better health.

297 Using the SF-12 also allows for conversion to utility scores which can also facilitate the  
298 undertaking of an economic analysis.

299

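### The QALY method is fixed as area under the curve, but QALY gain is not defined and no adjustment for baseline utility is named; adjusting would improve precision at no cost

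*Protocol*

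**What the plan says.** The protocol's Economic analysis section sets out the within-trial QALY calculation in sequence. SF-12 responses are converted to SF-6D utilities. The next step begins "To calculate the quality-adjusted life years (QALY) gain over the entire follow-up period" and names the method: "an 'area under the curve' methodology will be used [53". An incremental cost-effectiveness ratio follows. Uncertainty is shown on "cost-effectiveness planes generated from 1,000 bootstrapped resamples of the data", and acceptability curves come from bootstrapped net benefit. The SF-12 paragraph under Study Outcomes states the same purpose for the instrument.

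The Design section puts assessments at "baseline, post 12 weeks and 9 months". The Randomisation section says that envelopes are opened only after participants "consent to take part, and baseline measurements are completed", and it names no stratification factor. Baseline utility is therefore known before allocation.

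Two things are absent from the economic text. QALY *gain* is not defined: it could be the total area under the utility curve, or that area less what baseline utility alone would have given. And no covariate, regression or baseline term appears at any step from utilities to acceptability curves.

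**The concern.** Baseline utility is the first point of the curve and is correlated with the later points. If arms are compared on total area, a chance baseline difference passes into the incremental QALY in the same direction. If they are compared on area minus baseline, regression to the mean passes part of it on in the opposite direction. The two readings of *gain* therefore respond to the same imbalance with opposite signs, and neither removes it.

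The incremental QALY is the denominator of the cost-effectiveness ratio and enters net benefit directly. The protocol itself warns that quality-of-life differences may not show in a study of this size, yet it offers the acceptability curves as an input to decisions on wider adoption. With a small expected effect, avoidable noise in this quantity matters.

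**Working it through.** The protocol gives no utility, QALY or cost figure, so there is none to reproduce.

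**Inputs from the protocol.** 68 randomised per arm; assessments at baseline, about 3 months and 9 months, taken as 0, 0.25 and 0.75 years from baseline.

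**Assumptions.** SF-6D SD 0.12 at each visit (range 0.10 to 0.15); equal correlation 0.6 between any two visits (range 0.5 to 0.7); complete data.

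**Curve weights (trapezoid).** Baseline 0.25/2 = 0.125; 3 months 0.75/2 = 0.375; 9 months (0.75 − 0.25)/2 = 0.25. They sum to 0.75 years. Using 12 weeks exactly gives 0.115, 0.375 and 0.260, which changes little.

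**Slope on baseline utility.**
- Total area: 0.125 + (0.375 + 0.25) × 0.6 = 0.50.
- Area minus baseline (area − 0.75 × baseline): 0.50 − 0.75 = −0.25.

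**SE of the baseline difference.** 0.12 × √(2/68) = 0.0206.

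**Variance factors, in units of SD².**
- Total area: (0.125² + 0.375² + 0.25²) × 0.4 + 0.75² × 0.6 = 0.0875 + 0.3375 = 0.425.
- Area minus baseline (weights −0.625, 0.375, 0.25, which sum to zero): 0.59375 × 0.4 = 0.2375.
- Baseline-adjusted: 0.425 − 0.50² = 0.175, and equally 0.2375 − 0.25² = 0.175.

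| Estimator | SE of incremental QALY | Shift over the 95% chance range of the baseline difference | Variance saved by adjusting |
|---|---|---|---|
| Total area | 0.0206 × √0.425 = 0.0134 | 1.96 × 0.0206 × 0.50 = ±0.020 | 1 − 0.175/0.425 = 59% |
| Area minus baseline | 0.0206 × √0.2375 = 0.0100 | 1.96 × 0.0206 × 0.25 = ±0.010, reversed | 1 − 0.175/0.2375 = 26% |
| Adjusted for baseline | 0.0206 × √0.175 = 0.0086 | none expected | – |

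**Scale.** A utility benefit of 0.03 at both follow-ups is worth (0.375 + 0.25) × 0.03 = 0.019 QALY.

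**Range.** Over SD 0.10 to 0.15 and correlation 0.5 to 0.7:
- Total area: the slope runs from 0.4375 to 0.5625, the shift from 0.015 to 0.028, and the variance saving from 49% to 69%.
- Area minus baseline: the slope runs from −0.3125 (correlation 0.5) to −0.1875 (correlation 0.7). The shift runs from 1.96 × 0.0171 × 0.1875 = 0.006 to 1.96 × 0.0257 × 0.3125 = 0.016. The saving runs from 0.0352/0.1781 = 20% to 0.0977/0.2969 = 33%.

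**Simulation check under different assumptions.** 5,000 trials, 68 per arm, SD 0.10, correlation 0.6, utility effect 0.02, true gain 0.625 × 0.02 = 0.0125 QALY:
- All three estimators averaged 0.0124 to 0.0127, so none is biased overall.
- Their SDs were 0.0111 (total area), 0.0085 (area minus baseline) and 0.0072 (adjusted).
- In trials where the intervention arm started more than one SE lower, the means were about 0.000, 0.020 and 0.013 respectively.
- The chance of a negative incremental QALY was 12.7% for total area and 3.8% with adjustment.

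**The case against.** The strongest reply is that the protocol is silent rather than wrong. Area under the curve says how each participant's QALYs are built from utilities, not how arms are compared. Regressing those QALYs on arm and baseline utility is still an area-under-the-curve analysis and fits the bootstrapped net-benefit approach. A statistical or health-economic analysis plan, not shown here, may already provide for it. This stands: a reader might infer that the protocol prescribes a raw, unadjusted comparison, but no sentence says so or rules adjustment out.

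Two further points stand. Baseline is measured before random allocation, so an unadjusted difference is unbiased over repeated randomisations. And bootstrap replicates are centred on the observed imbalance but each has its own; their spread already reflects baseline sampling variation. The planes and curves would be less precise, not invalid.

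A reader might also infer that chance imbalance could decide the cost-effectiveness conclusion. The protocol does not support that: it gives no costs and no threshold value for a QALY, the economic evaluation is not the primary endpoint, and its wording is tentative.

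What the reply does not remove is that the section fixes the utility conversion, the QALY method, the number of resamples and the net-benefit approach, yet leaves its central quantity undefined and passes over a more efficient estimator that uses data already in hand.

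**Conclusion.** The point holds as a free improvement, not as an error in the stated text. Followed as written, with no baseline term, the analysis gives an incremental QALY that is less precise than it need be and is biased conditional on whatever baseline imbalance occurs. The direction of that bias depends on which meaning of *gain* is used.

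The sizes in the table rest on an assumed SF-6D SD and correlation. The existence of the precision gain does not depend on the exact values within the ranges tried. With fewer analysed participants the standard errors rise: at 50 per arm the ±0.020 becomes about ±0.024, while the proportional variance savings stay the same. If last observation carried forward were applied to utilities, which the protocol does not state, correlation with baseline would rise, and so would the carry-through for total area.

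**What to change.** Add one sentence to the Economic analysis section, or to the health-economic analysis plan if there is one: the incremental QALY is the arm coefficient from a linear regression of area-under-the-curve QALYs on arm and baseline SF-6D utility, and this regression is refitted within each of the 1,000 bootstrap resamples that feed the cost-effectiveness plane and the acceptability curves.

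This also settles the meaning of *gain*. Once baseline utility is in the model, total area and area minus baseline give the same arm coefficient, because the two outcomes differ only by a fixed multiple of the covariate. Baseline SF-12 is already collected before allocation, so the change needs no new data, visits or participants, only a few lines of analysis code.
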